### Gender and age selection

Adults of all genders equal or above 18 years are eligible for this clinical trial.

### Tumor imaging

For tumor assessment according to RECIST version 1.1 whenever possible, MRI should be chosen as examination method. However, conventional CT is permitted as alternative. The examination method once selected is to be retained for all examinations within the context of the study. Chest CT and additional skeletal scintigraphy /X-ray images of all affected bones in case of suspected bone metastases and additional cranial MRI or CT (MRI preferred whenever possible) in case of suspected CNS metastases are to be implemented. Additional imaging may be required in symptomatic patients if clinically indicated.

### Treatment regimen

Dosage and schedule were selected according to the results of Phase I study of FTD/TPI Plus Irinotecan and Bevacizumab in Advanced Gastrointestinal Tumors (Varghese AM et al.) [20].

FTD/TPI will be administered at a dose of 25 mg/m^2^ / dose twice daily on days 1–5 followed by a 9-days recovery period from day 6 trough day 14 of each 14-days treatment cycle.

The dosage is calculated according to body surface area (BSA) as displayed in Table 2. The dosage must not exceed 60 mg/dose. Table 2 also displays the necessary number of 15 mg and 20 mg tablets Lonsurf® to be taken. If any doses are missed, these doses must not be made up by the patient.

**Table 2 Tab2:** Calculation of dosing for FTD/TPI in mg according to BSA used in the TRITICC trial

**Starting dose** **25 mg/m**^**2**^	**BSA (m**^**2**^**)**	**Dose in mg** **2 × daily**	**Tablets per dose**		**Total daily dose (mg)**
			**15 mg**	**20 mg**	
	< 1.10	25!	2!	1!	50!
	1.10 – 1.29	30	2	0	60
	1.30 – 1.49	35	1	1	70
	1.50 – 1.69	40	0	2	80
	1.70 – 1.89	45	3	0	90
	1.90 – 2.09	50	2	1	100
	2.10 – 2.29	55	1	2	110
	> 2.30	60	0	3	120

(!) At a total daily dose of 50 mg, patients should take 1 × 20 mg tablet in the morning and 2 × 15 mg tablets in the evening

Irinotecan will be administered at the same time as FTD/TPI on day 1 of each cycle at a dose of 180 mg/m^2^ / dose.

Treatment will be administered until radiological progress or inacceptable toxicity.

#### Dose modifications and dose delays

Toxicity is classified according to NCI-CTCAE version 5.0; the dose modifications are made based on the grading given in the latter. The treatment must not be modified if adverse reactions occur which, according to the investigator's estimation, do not result in severe or life-threatening consequences (e.g. alopecia). Should several different toxicities appear simultaneously, the respective greatest dose reduction decrement should be applied. If an adverse reaction is unequivocally attributable to only one of the cytostatic agents the dosages of the other substances do not need to be modified. A further dose escalation is not permitted.

In case permanent discontinuation or treatment interruption of more than two cycles of one of the substances is required due to toxicity, study treatment has to be terminated. The further treatment will be at the treating physician's discretion.

#### Dose modification of FTD/TPI

A maximum of 1 dose reduction level (20 mg/m^2^ BSA BID) is permitted for FTD/TPI. Table 3 displays the dose in mg to be taken twice daily calculated per m^2^ BSA. (Tables 4 and 5).

**Table 3 Tab3:** Calculation of dose reduction for FTD/TPI in mg according to BSA used in the TRITICC trial

**Starting dose** **20 mg/m**^**2**^	**BSA (m**^**2**^**)**	**Dose in mg** **2 × daily**	**Tablets per dose**		**Total daily dose (mg)**
			**15 mg**	**20 mg**	
	< 1.14	20	0	1	40
	1.15 – 1.34	25!	2!	1!	50!
	1.35 – 1.59	30	2	0	60
	1.60 – 1.94	35	1	1	70
	1.95 – 2.09	40	0	2	80
	2.10 – 2.34	45	3	0	90
	> 2.35	50	2	1	100

(!) At a total daily dose of 50 mg, patients should take 1 × 20 mg tablet in the morning and 2 × 15 mg tablets in the evening

**Table 4 Tab4:** Dose interruption and resumption criteria for haematological toxicities related to myelosuppression [21]

**Parameter**	**Interruption**	**Resumption criteria**^**a**^
Neutrophils	< 0.5 × 10^9^/L	< 1.5 × 10^9^/L
Platelets	< 50 × 10^9^/L	> 75 × 10^9^/L

^a^Resumption criteria applied to the start of the next cycle for all patients regardless of whether or not the interruption criteria were met

**Table 5 Tab5:** Recommended dose modifications for FTF/TPI in case of haematological and non-haematological adverse reactions [21]

**Adverse reaction**	**Recommended dose modifications**
• Febrile neutropenia	• Interrupt dosing until toxicity resolves to Grade 1 or baseline
• Grade 4 neutropenia (< 0.5 × 10^9^/L) or thrombocytopenia (< 25 × 10^9^/L) that results in more than 1 week’s delay in start of next cycle	• When resuming dosing, decrease the dose level by 5 mg/m^2^/dose from the previous dose level
• CTCAE version 4 non-haematologic Grade 3 or Grade 4 adverse reaction; except for Grade 3 nausea and/or vomiting controlled by antiemetic therapy or diarrhoea responsive to antidiarrhoeal medicinal products	• Dose reductions are permitted to a minimum dose of 20 mg/m^2^/dose BID daily • Do not increase dose after it has been reduced

Dose escalation of FTD/TPI is not permitted after it has been reduced.

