### Inclusion criteria

Written informed consent incl. participation in translational research and any locally-required authorization (EU Data Privacy Directive in the EU) prior to performing any protocol-related procedures, including screening evaluationsAge ≥ 18 years at time of study entryHistologically or cytologically confirmed, non-resectable, locally advanced or metastatic cholangiocarcinoma or gall bladder carcinomaMeasurable or assessable disease according to RECISTDocumented disease progression after prior gemcitabine or gemcitabine containing therapy. Examples of permitted therapies include, but are not limited to: a) Single agent gemcitabine); b) Any gemcitabine-based regimen, with or without maintenance gemcitabineECOG performance status 0–1Ability to take medications orallyAdequate blood count, liver-enzymes, and renal function:ANC > 1,500 cells/μL without the use of hematopoietic growth factors; and Platelet count ≥ 100 × 109/L (> 100,000 per mm3) and Hemoglobin > 9 g/dL (blood transfusions are permitted for patients with hemoglobin levels below 9 g/dL)Serum total bilirubin ≤ 1.5 × upper normal limit (ULN) (biliary drainage is allowed for biliary obstruction; elevated bilirubin should be caused by obstruction not impaired liver function as assessed by albumin and INR values):Albumin levels ≥ 3.0 g/dLPatients not receiving therapeutic anticoagulation must have an INR < 1.5 ULN and PTT < 1.5 ULN within 7 days prior to inclusion. The use of full dose anticoagulants is allowed as long as the INR or PTT is within therapeutic limits (according to the medical standard in the institution) and the patient has been on a stable dose for anticoagulants for at least three weeks at the time of inclusion.AST (SGOT) and ALT (SGPT) ≤ 5 × institutional upper limit of normalSerum Creatinine ≤ 1.5 × ULN and a calculated glomerular filtration rate ≥ 30 mL per minute Adequate renal and bone marrow functionIn case of liver cirrhosis: Child–Pugh AWomen of childbearing potential must have a negative pregnancy test and must agree to adequate birth control if conception is possible. Males must agree to adequate birth control

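### Table 4 prints the neutrophil resumption limit in the wrong direction, so low counts qualify for the next cycle and recovered counts do not

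*Protocol article*

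**What the plan says.** The section on dose modification of FTD/TPI contains Table 4, which has an interruption column and a resumption column.

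- The neutrophil row reads "Neutrophils < 0.5 × 10^9^/L < 1.5 × 10^9^/L".
- The platelet row below it reads "Platelets < 50 × 10^9^/L > 75 × 10^9^/L".
- The footnote to the resumption column reads "Resumption criteria applied to the start of the next cycle for all patients regardless of whether or not the interruption criteria were met".

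Three other places bear on the same decision.

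- The inclusion criteria require "ANC > 1,500 cells/μL without the use of hematopoietic growth factors".
- Table 5 triggers a dose reduction for "Grade 4 neutropenia (< 0.5 × 10^9^/L) or thrombocytopenia (< 25 × 10^9^/L) that results in more than 1 week’s delay in start of next cycle".
- For febrile neutropenia, Table 5 says "Interrupt dosing until toxicity resolves to Grade 1 or baseline".

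The article gives no other neutrophil limit for starting a cycle.

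**The concern.** A resumption criterion should describe recovery, so for a blood count it should be a lower limit. The neutrophil row has an upper limit instead. Read literally, it allows redosing while the count is low and withholds treatment once the count has recovered.

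Because of the footnote, the criterion is not confined to patients who had to interrupt. It is the gate for every next cycle in every patient. Irinotecan 180 mg/m² is given on the same day 1 as FTD/TPI, and growth factors should not be used as prophylaxis, so the count gate carries much of the protection against neutropenic complications. An inverted gate puts patient safety at stake. It also puts at stake the adverse event data, which are a secondary endpoint, and the dose actually delivered.

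**Working it through.** The article states no figure to reproduce here. The check is one of logic, with a short count of how often the rule applies.

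**Step 1. Apply the printed criteria to a range of counts.** Interrupt if the count is below 0.5; resume if it is below 1.5 (both × 10^9/L, Table 4). The last two columns show a lower limit of 1.5 and the entry criterion (above 1,500 cells/μL, which is 1.5 × 10^9/L).

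| Neutrophils (× 10^9/L) | Interrupt | Resume as printed | Resume if ≥ 1.5 | Meets entry criterion |
|---|---|---|---|---|
| 0.2 | yes | yes | no | no |
| 0.49 | yes | yes | no | no |
| 0.5 | no | yes | no | no |
| 1.0 | no | yes | no | no |
| 1.49 | no | yes | no | no |
| 1.5 | no | no | yes | no |
| 1.51 | no | no | yes | yes |
| 2 | no | no | yes | yes |
| 4 | no | no | yes | yes |

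The interruption range (below 0.5) lies wholly inside the printed resumption range (below 1.5). Every count that meets the entry criterion fails the printed resumption criterion, so a patient whose count stayed at entry level could not start cycle 2.

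**Step 2. Apply the platelet row in the same way.** Interrupt below 50; resume above 75. Counts of 20 and 49 interrupt and do not resume, 50 and 75 do neither, and 76 and 150 resume. There is no overlap, and resumption means recovery.

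**Step 3. Compare with Table 5.** Its dose reduction rule depends on Grade 4 neutropenia having delayed the next cycle by more than a week. Table 4 as printed imposes no delay at low counts. Table 5's hold for febrile neutropenia likewise treats recovery as the condition for resuming. Both fit a lower limit and conflict with an upper one.

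**Step 4. Find where the error has least to stop it.** At 0.3, the interruption and resumption criteria visibly clash, and a reader may notice. At 0.8, the interruption criterion does not apply and the printed resumption criterion is met. For an afebrile patient, no other count-based rule in the article holds back the next cycle. Table 6 (irinotecan) sets dose levels by grade and occurrence but names no count to be reached before restarting.

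**Step 5. Count the decisions governed.** The section on study duration expects about 4 months of treatment, and cycles last 14 days. Taking 30.4 days per month:

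- Cycles per patient: 4 × 30.4 / 14 = 8.7
- Next-cycle starts per patient: 8.7 − 1 = 7.7
- With 25 patients (28 less the 3 allowed for drop-outs and invalid cases): 25 × 7.7 ≈ 190
- With all 28 patients: 28 × 7.7 ≈ 215

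**The case against.** The strongest reply is that this is a plain misprint whose intended direction any oncologist would recover from the platelet row, the column heading and Table 5. A rule that blocked every recovered patient could not be followed in practice. That is probably right about the cause. It does not settle whether the limit is above 1.5 or at least 1.5, and a dosing rule should not depend on readers reversing its sign.

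A second reply is that other rules protect the patient with a count of 0.3. For a first Grade 4 event, Table 6 recommends permanently stopping irinotecan, unless continuing is in the patient's best interest, at half dose and after consulting the coordination centre. The general rules on dose modification end study treatment if one agent is permanently stopped for toxicity. This reply stands in part: at 0.3 the next cycle would not simply proceed. But Table 6 is a recommendation for irinotecan, Table 5 expects FTD/TPI to be resumed after Grade 4 neutropenia, and the Grade 4 rule does not reach counts from 0.5 to 1.5.

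Third, sites work from protocol V03F, which is not shown and may carry the right sign. The article appeared on 22 May 2023, and recruitment was due to last 18 months from Q3 2021. On that schedule most cycle starts came before publication, although the last visit was still expected in August 2023. This limits what can be said about actual harm. It does not make the printed rule correct.

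Two smaller points also stand. An entry threshold and a redosing threshold need not be equal, so the entry criterion indicates the likely intended value but does not prove it. Also, interruption and resumption apply at different times, so the core defect is the reversed direction; the overlap is its symptom.

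A fault in the text extraction cannot be fully excluded. It is unlikely, because the greater-than sign is intact in the next row of the same table.

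**Conclusion.** The concern holds. As printed, Table 4 releases patients with neutrophils below 1.5 × 10^9/L for the next cycle and holds back those at or above it. This contradicts the direction of the platelet row and the delay and recovery rules in Table 5, and nothing in the article corrects it. The rule covers all patients at every next-cycle start, about 190 to 215 decisions if the expected 4 months on treatment is right. The article gives no incidence of neutropenia, so the number of decisions that would be changed cannot be estimated.

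The sample size and the method for the primary endpoint are not affected. Any effect on delivered dose, and through it on progression-free survival, is possible but not shown. The intended direction is inferred from the article alone, because neither V03F nor the source cited for the table was available. It must be fixed because it is a wrong dosing threshold in the treatment rules.

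**What to change.** Correct the neutrophil row of Table 4 to read: interrupt below 0.5 × 10^9/L; resume at or above 1.5 × 10^9/L, or strictly above 1.5 if the sponsor wants the form of the platelet row and the entry criterion. With either version no count meets both criteria; they differ only at exactly 1.5.

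The sponsor should first check the direction and limit against protocol V03F of 09.08.2021.

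- If only the article is wrong, publish a correction.
- If V03F carries the same sign, notify all sites at once and review the day-1 neutrophil counts for cycles already given.

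The cost is one symbol in a table and a short notice. The review of counts is extra work only in the second case.

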#### Dose modification of irinotecan

Table 6 displays recommended dose modifications for Irinotecan in case of haematological or non-haematological adverse reactions.

**Table 6 Tab6:** Recommended dose interruption/ modification criteria

	**Grade 2**	**Grade 3**	**Grade 4**
1st occurence	No dose recuction, prophylaxis if possible	75% of the initial dose, prophylaxis if possible	Permanent discontinuation, unless continuation of treatment is in the patients best interest; if so 50% of the inizial dose following consultation with the study coordination centre
2nd occurence	75% of the initial dose	50% of the initial dose	
3rd occurence	50% of the initial dose	Definitive withdrawal, unless continuation of treatment is in the patients best interest	
4th occurence	Permanent discontinuation, unless continuation of treatment is in the patients best interest		

#### Concomitant medication

All medication, which is considered necessary for the patient’s welfare, and which is not expected to interfere with the evaluation of FTD/TPI, may be given at the discretion of the investigator. All concomitant medications must be recorded in the patient’s source documentation, as well as in the appropriate pages of the eCRF. Subjects should receive full supportive care, including transfusions of blood and blood products, anti-infective drugs, and antiemetics when appropriate.

All patients should be closely monitored for side effects of all concomitant medications regardless of the path of elimination.

#### Antiemetics

During the treatment with FTD/TPI and Irinotecan, owing a moderate emetic potential, an antiemetic treatment should be administered according to center-specific protocols using, among others, dexamethasone and 5-HT3 antagonists. In case of insufficient effect, aprepitant (Emend®) may be considered. Appropriate prophylactic antiemesis is recommended.

#### Anticoagulants

The use of full dose anticoagulants is allowed as long as the INR or PTT is within therapeutic limits (according to the medical standards in the institution) and the patient has been on a stable dose for anticoagulants for at least two weeks at the time of registration. During treatment close monitoring of INR for oral anticoagulants is recommended.

#### Growth factors

Hematopoietic growth factors (i.e., G-CSF) may be used according to institutional guidelines to treat febrile neutropenia, but should not be used as primary or secondary prophylaxis. Growth factors must be discontinued at least 48 h prior to initiation of the next treatment of chemotherapy.

#### Prohibited concomitant medication

The following medications/treatments are not allowed during the study participation, unless the patient is in the follow-up phase and has permanently discontinued any study medication:

Any investigational medicinal product or experimental therapy or participation in another clinical trial. Any other anti-tumor treatment including chemotherapy, targeted therapy, antibodies, any antihormonal tumor treatment, and immunotherapy other than FTD/TPI and Irinotecan.

Current data in gastric cancer indicate a potential worse survival for patients receiving fluoropyrimidine-derivates with the concomitant use of protone-pump inhibitors, which should be avoided if possible. For details of contraindications, Investigators should refer to the respective SmPC. Caution is required when using medicinal products that are human thymidine kinase substrates, e.g., zidovudine. Such medicinal products, if used concomitantly with FTD/TPI, may compete with the effector, trifluridine, for activation via thymidine kinases. Therefore, when using antiviral medicinal products that are human thymidine kinase substrates, monitor for possible decreased efficacy of the antiviral medicinal product, and consider switching to an alternative antiviral medicinal product that is not a human thymidine kinase substrate, such as lamivudine, and abacavir. It is unknown whether FTD/TPI may reduce the effectiveness of hormonal contraceptives. Therefore, women using hormonal contraceptive must also use a barrier contraceptive method.

### Statistical considerations

The primary endpoint, time till progression-free survival, will be analyzed using a non-parametric survival estimate. To this end the method of Turnbull will be used to compute the survival curve [22]. The variance of the survival will be estimated using the Greenwood formula. The log transformation will be used for the calculation of confidence intervals.

An exploratory analysis of secondary outcomes will be performed. Overall survival will be analyzed using the Kaplan–Meier estimate of survival. For the secondary outcomes, objective response and occurrence of adverse events the proportion of patients with the outcome and confidence intervals using the Wilson method will be calculated [23].

The statistical analysis will be carried out by the Coordination Center for Clinical Trials Düsseldorf (KKSD).

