**2. Endpoints**
**2.1 Primary Endpoint** • Median progression free survival (PFS) assessed by the local investigator

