### Sample size determination

Sample size consideration for this study is based on the precision of the survival estimate for the outcome progression-free survival. Based on previous results with the combination of Irinotecan and 5-FU therapy in patients with biliary tract cancers we assume a median survival time of 3 months. Assuming an exponential failure time with a median survival of 3 months (hazard rate: 0.23 per month) and a censoring rate of 0.04 per month, a total sample size of 28 patients (including 3 calculated drop outs and invalid cases) results in an expected standard error of 0.09 for the 3 months survival.

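### The primary PFS curve is Turnbull's interval-censored estimate, but its variance is Greenwood's, which is too small once scan intervals overlap

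*Protocol article*

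**What the plan says.** Table 1 of the protocol article gives the primary endpoint as "Median progression free survival (PFS) assessed by the local investigator". For its analysis, Statistical considerations specifies a non-parametric estimate: "the method of Turnbull will be used to compute the survival curve". Two further sentences follow: "The variance of the survival will be estimated using the Greenwood formula" and "The log transformation will be used for the calculation of confidence intervals". The Discussion, under Sample size calculation, repeats all three choices. Overall survival is assigned to Kaplan-Meier, so Turnbull for PFS reads as a deliberate decision to treat progression as interval-censored.

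Sample size determination justifies the 28 patients (25 after 3 drop-outs and invalid cases) only by precision, with an expected standard error of 0.09 for 3-month PFS. The article states no test, success threshold, confidence level or restaging interval.

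**The concern.** Greenwood's formula is Var S(t) = S(t)² × Σ dᵢ / [Yᵢ(Yᵢ − dᵢ)], summed over known event times, with dᵢ events among Yᵢ patients at risk. It belongs to the product-limit estimate.

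In Turnbull's method, a patient who progressed between scans at L and R contributes S(L) − S(R) to the likelihood. With overlapping intervals there are no observed dᵢ or Yᵢ, only expected counts allocated by the algorithm. Putting those into Greenwood treats allocated progressions as observed ones and ignores the information lost between scans, so the SE comes out too small.

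Overlap is to be expected here. Tumor imaging allows extra scans in symptomatic patients, the dose rules allow delays, and up to 6 centres take part. Deaths counted as PFS events would be dated exactly. With no hypothesis test, the interval around the PFS estimate is the whole of the primary inference.

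**Working it through.** **Inputs from the article.** Median 3 months, so λ = ln 2 / 3 = 0.231 per month and S(3) = 0.50; "a censoring rate of 0.04 per month", so c = 0.04; n = 28 or 25.

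**Assumed, because the article is silent.** Two-sided 95% level; scans every 1.4 to 2.8 months; visit shifts up to ±0.25 month; 0 to 10% missed visits; 0 to 20% of events dated exactly; linear interpolation inside Turnbull's intervals.

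**The plan's own figure.** For right-censored exponential data, SE² = S² × λ / [n(λ + c)] × (e^{(λ+c)t} − 1).
- (λ + c)t = 0.271 × 3 = 0.813 and e^0.813 − 1 = 1.255.
- λ/(λ + c) = 0.852, so n × SE² = 0.25 × 0.852 × 1.255 = 0.267.
- SE = √(0.267/28) = 0.098, or √(0.267/25) = 0.103.

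The stated 0.09 is not reproduced. A binomial SE with all 28 patients and no censoring, √(0.25/28) = 0.094, would round to it. That is a small separate point. What matters here is that these formulas all assume exactly observed event times.

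**Does Greenwood describe the Turnbull estimate?** Simulation with 3,000 replicates per row, exponential PFS and Greenwood on the allocated counts. S(3) = 0.50, so coverage at 3 months is also coverage of the inverted interval for the median. Info SE is the observed-information SE. Coverage is for plain-log intervals; its Monte Carlo error is about √(0.89 × 0.11/3000) = 0.6 points.

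| n | Scans every (months) | Shift | Missed | Exact deaths | True SD | Greenwood SE | Ratio | Coverage, Greenwood | Info SE | Coverage, info |
|---|---|---|---|---|---|---|---|---|---|---|
| 28 | 2.0 | ±0.25 | 0 | 0 | 0.1225 | 0.0969 | 0.79 | 88.9% | 0.1199 | 92.0% |
| 28 | 2.0 | ±0.10 | 0 | 10% | 0.1264 | 0.0965 | 0.76 | 87.3% | 0.1170 | 90.7% |
| 28 | 2.0 | ±0.25 | 10% | 20% | 0.1246 | 0.0970 | 0.78 | 88.8% | 0.1163 | 92.1% |
| 28 | 1.4 | ±0.25 | 10% | 20% | 0.1138 | 0.0969 | 0.85 | 92.2% | 0.1073 | 93.5% |
| 28 | 2.8 | ±0.25 | 10% | 20% | 0.1243 | 0.0977 | 0.79 | 90.3% | 0.1178 | 93.4% |
| 25 | 2.0 | ±0.25 | 10% | 20% | 0.1324 | 0.1022 | 0.77 | 87.2% | 0.1210 | 90.3% |
| 28 | 2.0, common grid (read at 4 months) | 0 | 0 | 0 | 0.0993 | 0.0966 | 0.97 | 94.3% | 0.0966 | 94.3% |

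A smaller run (1,500 replicates) of the 1.4-month setting gave ratio 0.90 and coverage 93.7%. Separate runs with scans every 1.84 months, shifts of ±0.1 to 0.23 month and 10 to 15% exact deaths gave SD 0.121 to 0.122 against Greenwood 0.097, with 86 to 88% coverage. Those runs also gave 90% with 2.76-month scans, 94% with 1.4-month scans and 96% on a common grid without exact deaths.

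**The log scale.** With S = 0.5 and SE 0.0977:
- Plain log: 0.5 × exp(±1.96 × 0.0977/0.5) = 0.341 to 0.733.
- Log-log: 0.5^exp(±1.96 × 0.0977/(0.5 × 0.693)) = 0.300 to 0.671.

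With exact times and Kaplan-Meier (20,000 replicates, n = 28), plain log puts the lower limit too high in 5.4% of trials and the upper too low in 0.7%. Log-log gives 1.4% and 3.8%. At n = 25, plain log puts the lower limit too high in 5.8%. Under Turnbull with Greenwood, 2-month scans and n = 28, coverage is 87 to 89% with plain log and 88 to 89% with log-log. Changing the scale moves the misses from one side to the other and does not cure the variance.

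**The case against.** The strongest reply is that the effect is conditional. On a common scan grid with nothing missed and no exact deaths, Turnbull's estimate equals a grouped Kaplan-Meier at the scan times and Greenwood works. The article gives no restaging interval, so every coverage figure rests on an assumed one. It also rests on an interpolation rule, because Turnbull's curve is undefined inside its intervals. All of this stands. It limits the size of the effect and leaves the mismatch in the text untouched.

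Second, this is an exploratory single-arm phase IIA trial without a decision threshold, and neither Greenwood nor the log scale changes the Turnbull point estimate. This also stands and bears on severity.

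A reader might infer three stronger things that the documents do not support:
- That the limits are certain to be too narrow. The common-grid case shows otherwise.
- That they are also misplaced in the treatment's favour. Plain log is only the natural reading of the article's wording, and with 2.8-month scans the misses were even (4.7% and 4.9%).
- That a parametric model must replace the primary estimate. An interval-censored Weibull covered 95% in 400 runs and 93.1% in 1,200, with the lower limit too high in 5.4% of the latter. Those runs used exponential data, for which the Weibull shape is correct. The article chooses a non-parametric estimate, and these results are no reason to overturn that.

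**Conclusion.** The concern holds in conditional form. Greenwood's formula does not match the stated primary estimator. At n = 28, with overlapping scan intervals, its SE for 3-month PFS is generally about 10 to 24% too small, and nominal 95% intervals cover roughly 86 to 94%. These figures assume exponential PFS with the protocol's median and censoring rate, scans every 1.4 to 2.8 months, and linear interpolation. The log scale is secondary. Severity: should-fix. The interval is the trial's only primary inference, but the point estimate is unaffected and the correction can be made before analysis without touching design or data collection.

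**What to change.** In Statistical considerations, and where the Discussion repeats it:
- Keep Turnbull's estimate as the primary PFS curve and delete Greenwood for it.
- Take the confidence limits for the curve and for median PFS from a method valid for interval-censored data: observed-information or likelihood-based, or a patient-level bootstrap. State the confidence level and the interpolation rule.
- Say that coverage remains approximate at this size. The information-based SE gave 91 to 94% at n = 28 and 90% at n = 25. A percentile bootstrap gave 90% in 400 runs.
- Use Greenwood only with Kaplan-Meier: for overall survival, or for PFS on scan dates as a sensitivity analysis. Name the log-log scale there. PFS on scan dates runs late: with assumed 8-weekly scans its median was 3.7 months for a true 3.0.
- Optionally add an interval-censored Weibull median as a sensitivity analysis, with its shape assumption declared.

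The cost is revised wording, a little more code and wider intervals. In the overlapping rows of the table the information SE exceeds Greenwood's by about 11% (0.1073/0.0969) to 24% (0.1199/0.0969).
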